### Interventions

The interventions being evaluated, SCR and CCR, differ solely in the amount of carious dentine removed during the excavation phase of restorative treatment of deep dental caries. Clinicians will restore the tooth with the material that they would normally use. This may be amalgam or resin composite with or without glass ionomer cement. Placement of a separate pulp lining protection material is permitted. However, it should not be medicated i.e. including steroids or antibiotics. Information about any pulp protection material placed will be recorded.

#### Intervention: selective caries removal (SCR)

Gain access to the dentine caries by removing superficial enamel or existing restorationRemove caries from the periphery of the cavity to allow for good adaptation and seal to the restorationEither at the enamel dentine junction or the peripheral 2 mm of dentine if the cavity margin is on root dentine. Remove remaining carious dentine to soft dentine “that deforms when an instrument is pressed into it and can be easily scooped up (e.g. with a spoon hand excavator) with little force being required” [22]

#### Control: complete caries removal (CCR)

Gain access to the dentine caries by removing enamel or existing restorationRemove caries to firm dentine “physically resistant to hand excavation and some pressure needs to be exerted through an instrument to lift it” [22]

#### Training in the delivery of intervention

As the primary difference between the health technologies being assessed is the amount of carious dentine removed effective clinical training is of prime importance. The training will utilise a novel clinical learning tool, providing an on demand online resource and mechanisms for monitoring sustained delivery of the allocated technology.

All clinicians will participate in and complete the SCRiPT trial training (Part 1 hands-on in clinical procedures Part 2 Good Clinical Practice). Other members of the dental team will complete SCRIPT Part 2 which can be delivered remotely. Prior to the COVID-19 pandemic Part 1 training was provided in its entirety at hands-on clinical facilities. This included information on the background of operative caries management and trial interventions, together with hands on practice of both SCR and CCR on plastic teeth that have been 3D printed at different densities to replicate caries.

During the COVID-19 pandemic Part 1 training was re-designed to meet physical distancing guidelines by using a blended learning approach i.e. a combination of virtual theoretical training and a remote practical training exercise. Part 1 training was divided into part 1a and 1b. Part 1a covers the background to the interventions and description of the interventions, including video recordings of the interventions. This training was/is delivered remotely via Zoom meetings. Part 2a involves posting 3D plastic teeth to the dentists to complete the trial interventions and returning a selected pair of teeth to the trial clinical team for validation and to check adherence to protocol. In cases where further training was required this was followed up by individual zoom discussion, feedback and further practice on 3D printed teeth.

### Monitoring fidelity to protocol

Monitoring fidelity with the clinical protocol is essential to exclude merger of the clinical techniques and consistency of technology used when more than one tooth has a deep carious lesion. We will implement 3 strategies to assess compliance:Clinicians will be asked after every third patient to cut both a SCR and CCR cavity in two 3D computer generated sample teeth and return these to the research office. These teeth will be examined by a member of the clinical team to monitor compliance. If merger of SCR and CCR is observed additional training and or reinforcement of protocol will be providedThe CRF will include an assessment of colour, hardness and consistency to monitor whether SCR or CCR has been performed according to protocol. The lighter shade would be consistent with CCR, a darker shade with SCR. The hardness of the cavity will be assessed with a dental explorer/spoon excavator. Soft would indicate SCR and hard would indicate CCR. The CRFs will be assessed in real time to monitor fidelity and feedback will be provided if evidence of merger is observed.Baseline and 1-year follow-up bitewing radiographs will be assessed by a researcher masked to treatment group, to confirm the extent of initial caries and following the restoration the presence of caries. Follow up x-rays will be taken at intervals judged appropriate by the clinicians therefore assessment will be 6–12 months after treatment.

### Study recruitment and allocation

#### Recruitment of dentists

General dental practice is the main provider of NHS dental care. SCRIPT will recruit approximately 65 NHS dental practices (and up to 75 clinicians) from across the UK within the participating regions. A list of study sites will be available on the study website.

An open invitation will be distributed using routine NHS communication systems such as NHS Education for Scotland’s Portal, BDA section and Local Dental Committee networks to request expressions of interest. Practices that have successfully recruited to and delivered previous dental HTA trials will be targeted through our research networks. Also, the planned NIHR Clinical Research Network oral and dental specialty national questionnaire will be used to identify interested practices. Following the expression of interest, a trial briefing session will be delivered remotely, and an appraisal of each practice’s ability to recruit participants will be conducted.

#### Identifying and recruiting participants

The trial will aim to recruit 65 practices (each recruiting an average of 10 participants) to achieve the target of 623 participants. Trial clinicians will identify patients at routine visits that meet the inclusion criteria and explain the trial. Eligible patients who express interest will be given a participant information leaflet (Additional file 1) and an appointment for their treatment as per current clinical practice. At the treatment visit the patient will be given the opportunity to clarify any questions prior to informed consent being obtained and recorded on a written consent form (Additional file 2).

The eligibility of all participants will be assessed and determined by their dental practitioner following clinical and radiographic examination according to pre-determined criteria. Those who do not wish to take part will receive caries removal and restoration as per current practice. Those who are eligible and wish to take part will give informed consent to the clinician providing treatment.

A baseline questionnaire will be completed by the participant to collect baseline patient centered outcomes. Randomisation will then take place using an online randomisation system. If the participant has more than one eligible tooth, a trial tooth will be selected at random by the randomisation application. The randomisation algorithm will use recruitment site, number of eligible teeth (1; > 1) and type of caries (primary and secondary) as minimisation covariates to allocate to treatment intervention and control groups in a ratio of 1:1To maintain participant blinding, participants will not be informed of their allocated treatment group following randomisation. Baseline clinical information will be recorded by the clinician after the treatment has been provided.

After the initial intervention participants will receive any treatment deemed clinically appropriate by their dentist as per normal practice.

#### Inclusion criteria

Aged 12 years and over, suitable to receive either clinical procedure.Patients able to provide informed consentPatients receive some or all of their treatment under NHS
One (or more) pre-molar or molar teeth with caries (primary or secondary) extending into the pulpal third of dentine.Caries may be proximal and/or occlusal and the lesion will be suitable for a direct filling with a single restoration.

#### Exclusion criteria

If the carious tooth shows signs or symptoms of irreversible pulp pathology or loss of vitality including:The presence of a sinusTenderness to percussionBuccal tendernessPathological mobilitySevere sensitivityEvidence of pathology on a periapical radiograph

### Outcome measures

#### Primary outcome

ClinicalSustained tooth vitality

EconomicIncremental net benefit (WTP minus costs) over a modelled lifetime horizon

#### Secondary outcomes

ClinicalPulp exposure during caries removal;Progression of caries;Tooth restoration failure and re-restoration

Patient-centeredDental pain; need for dental pain relief;Health status; Oral Health-Related Quality of LifeOral health behavioursPatient satisfaction

EconomicGeneral population preferences,Willingness to payNHS and patient perspective costs collected over three years follow up, and modelled over a lifetime horizonQALYs and incremental cost per QALY over three years follow up, and modelled over a lifetime horizonIncremental net benefits over three years follow-up

## Data collection and processing

Participating dental practices will be expected to maintain a file of essential trial documentation which will be provided by the Trial Coordinating Office Dundee (TCOD).

Participants who lose capacity to consent during the study will be withdrawn. Identifiable data already collected with consent would be retained and used in the study. No further data will be collected or any other research procedures carried out on or in relation to the participant.

### Baseline characteristics

At baseline information will be collected on participants’ socio-demographic characteristics, generic health-related quality of life, oral health-related quality of life, oral health behaviours, and time and travel costs through a participant questionnaire. Oral health status and caries experience (DMFT) will be calculated by the clinician. Bitewing radiographs and periapical radiographs (if clinically needed) will be collected as part of routine care but copies will be provided to the trial team to provide a measure of the extent of caries and confirm exclusion of signs of pulp pathology. A case report form (CRF) will record the details of treatment including caries removal, restoration placed, and resources required to deliver the respective treatments. Any modification of or deviation from the intervention will be recorded on the CRF to inform the clinical outcomes.

### Clinical outcomes

Clinical outcomes will be recorded on the CRF completed by the clinician at the end of each course of treatment until the end of the trial. It will record clinical and participant-reported signs and symptoms of tooth pain, the findings of any radiographs taken, the reason for and detail of any dental treatment provided for included teeth. Radiographs taken during the trial will be taken according to good practice guidelines based on caries risk at intervals between 6 and 24 months. Clinicians will take a bitewing radiograph at one year post-treatment, in accordance with Faculty of General Dental Practitioners (FGDP) guidelines [23] since included patients are considered at high caries risk, at the follow-up visit and the trial team will request a copy for treatment adherence monitoring. If a participant has not received any post-intervention visit by 4 months before the end of the follow-up period, they will be contacted by the dental practice and offered an appointment. All radiographs will be assessed by a clinical researcher who is blinded to treatment allocation. Digital radiographs will be forwarded via the secure trial management system and digital images of wet films made.

***Sustained tooth vitality ***will be collected at routine dental visits, recorded in the CRF and used in a time- to-event framework defined as the time from randomisation to root canal treatment or extraction due to loss of vitality, the primary time point of interest is three years. Sustained tooth vitality will be determined by the absence of root canal treatment or extraction due to loss of vitality and the absence of clinical signs and symptoms of pulp death including evidence from radiographs.

***Pulp exposure during caries removal ***will be recorded by the clinician at the time of intervention. If soft tissue within the tooth is exposed this will be detected visually by bleeding and or a pink or red spot.

***Progression of caries ***will be clinically and radiographically assessed by the clinician at each visit as per national guidelines. An independent blinded assessor will also evaluate the radiolucent area on radiographs taken between baseline and follow-up.

***Tooth restoration failure and re-restoration ***will include the reason and subsequent treatment and will be collected at routine visits in a similar fashion to the primary outcome.

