## Methods/design

This is a pragmatic, primary dental care, multi-centre, single-masked, two-arm patient randomised controlld trial including an internal pilot, comparing the clinical-effectiveness and cost–benefit of Selective Caries Removal (SCR) with Complete Caries Removal (CCR) in permanent posterior teeth in participants aged 12 years and over.

Follow-up will last at least 3 years and will be conducted in multiple sites across the UK. The design includes an internal pilot to assess the recruitment of practices and participants and monitor compliance with the clinical protocol and acceptability for patients and clinicians (Fig. 1).

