## Analysis plan

### Sample size calculation

The sample size calculation is event-based. We aim to detect an absolute improvement in sustained tooth vitality at three years of 12% from 80% (CCR) to 92% (SCR). The control rate of 80% is based upon the existing evidence base, clinical experience and confirmed by Scottish tooth-level routine data. As described in Sect. 2.1 above, the current evidence base gives rates of pulpal exposure that are higher than those seen in UK NHS and therefore our rate of sustained tooth vitality will be higher than observed in those studies. Bjørndal 2017 [12] presented a tooth vitality rate of approximately 80% at 3 years for two-step selective restoration in lesions that were deeper than those in this trial. The two-step procedure is more similar to a CCR than the SCR in our trial. The Scottish tooth specific data demonstrated that of 459,648 teeth that required a three surface restoration in 2013, 6.6% had received further endodontic treatment or were extracted at 3 years follow-up. These teeth however, could be at any level of dentine involvement and it is not possible to identify the level of involvement in the routine data. Therefore, as the study is interested in only teeth with involvement in the pulpal third of dentine, it has been estimated that the number of events may be three times larger. There is little empirical evidence to inform the expected size of an important effect. A target difference of 12% was judged clinically important and plausible by both dentists and PPI partners. The target difference of 12% was also informed by the difference observed in Bjørndal 2017 [12] which was 13.7% at 5 years. However, as this is a patient RCT there are concerns around contamination (participants receive the intervention that they were not randomly allocated to). The team conservatively have allowed for up to 25% contamination and therefore the sample size for SCRiPT aims to detect an absolute improvement of 9%; from 83 to 92% at three years. Recruitment of 623 participants (71 events) will detect a hazard ratio of 0.42 between experimental and control strategies and provide, using the log-rank test, assuming an exponential failure rate, 90% power at a 2-sided 5% significance level. The calculation also assumes 17 months of recruitment, a minimum of 33 months of follow-up and a 30% follow-up attrition at the end of year three. Recruitment is assumed to be staggered and builds in seasonal variation. We used the Stata package ARTSURV for calculations [35].

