### Missing data

Strategies with proven effectiveness in improving retention will be used to minimise missing data [36]. For participants who do not return or are censored early in the trial, dental practices will be contacted to find out potential reasons for missing data if they are available.

Participants with no event will be censored at their last visit with sustained tooth vitality. It is anticipated that a small proportion of participants will not return at all, and a further proportion will be censored early in the trial because they do not come back to their clinician. The team will consider how robust the findings are to these missing data using multiple imputation approaches under an assumption of missing at random, and using pattern mixture models if appropriate. In participants with more than one eligible tooth, we will repeat our primary analysis with a clustering effect for participant.

Routinely collected data will be considered to supplement missing outcome data if deemed appropriate. We will undertake a validation analysis comparing (primary outcome) CRF data with routinely collected tooth-level data which will also provide the opportunity for secondary and economic outcome data analysis if the data are valid. This will be detailed in a data linkage analysis plan.

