## Milestones for the SCRiPT trial

Dental practice recruitment began at month 3. Patient recruitment has been delayed due to the effects of COVID-19 and has therefore not commenced on time. We predict that patient recruitment will take place over an 18-month period. Follow up assessments will take place three years after recruitment and delivery of intervention.

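### Table 1 schedules a 36-month vitality record, but the only stated recall rule omits participants who attended once and then stopped; they are censored at that visit

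*Protocol article*

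**What the plan says.** All places are in the protocol article.

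- **Schedule.** Table 1 (Scheduling of events) marks sustained tooth vitality for collection on the dental practice CRF at 36 months. Milestones agrees: "Follow up assessments will take place three years after recruitment and delivery of intervention".
- **Collection.** Clinical outcomes takes vitality from routine dental visits and names three years as the primary time point. It also sets a bitewing at one year.
- **Recall.** The same section has the practice contact the participant and offer an appointment under one condition: "If a participant has not received any post-intervention visit by 4 months before the end of the follow-up period".
- **Censoring.** Missing data states: "Participants with no event will be censored at their last visit with sustained tooth vitality". It expects some participants never to return and others to be censored early. It plans retention strategies, enquiries to practices, multiple imputation under missing at random, pattern mixture models if appropriate, and use of routine data if judged appropriate.
- **Duration.** Methods/design: "Follow-up will last at least 3 years". Sample size calculation: "The calculation also assumes 17 months of recruitment, a minimum of 33 months of follow-up", with 30% attrition by the end of year three.

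**The concern.** The recall condition is met only by people with no visit at all since treatment. One attendance, however early, removes a participant from it. The one-year bitewing makes such an attendance likely, so the rule can miss exactly the people who are seen in year one and not again. Nothing else in the article says how their 36-month record is obtained.

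Two alternative harms follow, depending on what happens to later failures.

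- If failures after the last visit are not recorded, follow-up and events are lost and power falls.
- If failures bring people back through pain while sound teeth do not, event-free time is cut short but events are kept. Vitality at three years is then read too low. The trial's time-to-event data are extrapolated in the lifetime economic model (Decision modelling), so absolute levels matter as well as the ratio.

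Separately, a 33-month minimum, if applied in conduct, would leave the last recruits short of the 36-month assessment.

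**Working it through.** **Inputs from Sample size calculation.** Event-free rates "from 83 to 92% at three years"; N = 623; 71 events; "using the log-rank test, assuming an exponential failure rate, 90% power at a 2-sided 5% significance level"; 17 months' recruitment; minimum 33 months; 30% attrition at three years. Allocation is 1:1.

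**My assumptions.** Uniform accrual, so follow-up runs uniformly from 33 to 50 months; exponential attrition; and the shares of participants who stop attending. The plan itself used staggered, seasonal recruitment.

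**1. The plan's own figure.** The hazard ratio implied by 83% and 92% is ln 0.92 / ln 0.83 = 0.447.
- Freedman: ((1 + 0.447)/(1 − 0.447))² × (1.960 + 1.282)² = 72.1, so 73 events.
- Schoenfeld: 4 × (1.960 + 1.282)² / (ln 0.447)² = 65.0, rounded up to 66 events.
- Monthly hazards: λ = −ln 0.83/36 = 0.00518 (CCR) and −ln 0.92/36 = 0.00232 (SCR). Attrition: g = −ln 0.70/36 = 0.00991.
- Expected events per arm: 311.5 × λ/(λ + g) × mean of [1 − exp(−(λ + g)T)], with T from 33 to 50. This gives 49.6 + 23.4 = 73.0.

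The stated 71 is reproduced to within two events. Schoenfeld power, Φ(√d/2 × |ln HR| − 1.960), is 93.0% at d = 73.0.

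**2. Lost follow-up.** Suppose a share q is last seen at month m, beyond the 30% attrition, and later events are not recorded. Then d = (1 − q) × 73.0 + q × d(m), where d(m) is the expected number if all 623 stopped at m: 25.75 at 12 months and 47.5 at 24.

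| Assumed share and last visit | Events | Power at HR 0.447 |
|---|---|---|
| 20% at 12 months | 63.5 | 89.3% |
| 30% at 12 months | 58.8 | 86.9% |
| 50% at 12 months | 49.4 | 80.6% |
| 30% at 24 months | 65.3 | 90.1% |

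At the plan's stated hazard ratio of 0.42, 58.8 events would give 91.4%.

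**3. Return only with symptoms.** Suppose a share q stops routine attendance, with last visit uniform over 0–36 months, and a fraction c of later events is still recorded. With S(t) the true survival and u = t/36:
- event density: λS(t)[(1 − q) + q(1 − u) + qcu];
- at risk: S(t)[(1 − q) + q(1 − u)] + qcu[S(t) − S(36)].

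The last term is there because recorded later events stay in the risk set until they occur. Integrating density over risk set to 36 months gives the Kaplan-Meier reading:

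| q | c | CCR | SCR | Difference (points) | ln SCR / ln CCR |
|---|---|---|---|---|---|
| truth | – | 83.0% | 92.0% | 9.0 | 0.447 |
| 30% | 1 | 80.3% | 90.6% | 10.3 | 0.450 |
| 50% | 1 | 77.6% | 89.2% | 11.5 | 0.452 |
| 30% | 0.5 | 81.6% | 91.3% | 9.7 | 0.449 |
| 30% | 0 | 83.0% | 92.0% | 9.0 | 0.447 |

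**4. Attendance differing by arm (c = 1).** Mean person-time to 36 months is (1 − S)/λ for attenders: 32.8 months (CCR) and 34.5 (SCR). For those who stop it is 18 × S less: 17.9 and 18.0.
- 20% stopping in CCR and 40% in SCR: person-time 29.9 and 27.9; rate ratio (0.08/27.9)/(0.17/29.9) = 0.50.
- The reverse: person-time 26.9 and 31.2; rate ratio (0.08/31.2)/(0.17/26.9) = 0.41.

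**5. Durations.** With a 36-month minimum and 17 months' accrual, expected events are 76.8 and power 94.1%, against 73.0 and 93.0%. Under uniform accrual, 3/17 × 623 = 110 participants would have less than 36 months.

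**The case against.** The strongest reply is that the three-year observation is planned: Table 1 schedules it and Milestones places assessments at three years. A reader might infer from the recall rule that no such observation is intended, and the documents do not support that. Nor do they say other contact is excluded, and a journal article may leave operational detail to the full protocol. What remains is that the article does state a recall trigger, and as worded it does not deliver the visit that Table 1 schedules.

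The plan also has mitigations. Most participants are described as routine attenders, 30% attrition is in the sample size, and sensitivity analyses and linkage are foreseen. These help only in part. The attrition allowance protects power, not the absolute estimates. Imputation under missing at random does not remove bias when attendance depends on the outcome. Pattern mixture models and routine data are conditional, and tooth-specific linkage is described for Scotland, with tooth-level data elsewhere only where possible.

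It is tempting to say that vitality will be biased downward in both arms. The documents do not establish this: it needs symptomatic return to a trial clinician, and it is zero if later events are not recorded. Silent failures seen only on radiographs would be missed by non-attendance and act the other way. The article gives no reason to expect attendance to differ by arm, and participants are masked.

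On durations, the 33 months is a planning input and conservative for power. The 18-month recruitment period in Milestones is a forecast made after the pandemic delay, so its difference from 17 months is not a contradiction of weight.

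**Conclusion.** The point holds as a mismatch between the 36-month record in Table 1 and a recall trigger too narrow to obtain it, combined with censoring at the last visit. It is a low-cost correction that protects the primary endpoint, not a fatal flaw.

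Its size depends on attendance, which the article does not quantify. Power drops below 90% at the implied hazard ratio of 0.447 if about 20% or more are last seen at 12 months beyond planned attrition and later events are lost. Under symptomatic return with 30% stopping, absolute vitality is understated by up to about 2.7 points (CCR) and 1.4 points (SCR). These two scenarios are alternatives and should not be added. The primary hazard ratio stays near 0.45 unless attendance differs by arm.

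The three-year and 33-month minima conflict in wording and need reconciling. This is not a power error. The figure of about 110 participants short of month 36 applies only if 33 months were used in conduct, and under uniform accrual.

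**What to change.** 1. Reword the trigger in Clinical outcomes so that practices contact every event-free participant with no recorded visit near the end of follow-up, for example within the last 6 months, and offer the 36-month assessment in Table 1. The 6-month window is a suggestion; the documents give no figure. The contact mechanism already exists, so the cost is additional recall contacts and appointments for practices.
2. State one minimum follow-up. Either set it to 36 months in Sample size calculation, or say there that 33 months is a conservative planning value and that each participant is followed to 36 months. This costs wording only; with a 36-month minimum, expected events rise from 73.0 to 76.8. If 33 months is really intended in conduct, Methods/design, Milestones and Table 1 must be changed to match.

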Bjørndal et al. [12] followed-up for 5 years a 2-staged (stepwise) carious tissue removal protocol on lesions spreading into the pulpal quarter of dentine (n=239). Pulp exposure rate was lower in this stepwise removal protocol (21.2% vs. 35.5%; p = 0.014) and more successful (60.2% vs 46.3%) (p = 0.031) when pulp exposures were classed as failure. The trial has limited generalizability to SCRIPT’s context and patients: it recruited participants with more severe caries and its two interventions differed from SCRIPT’s. Their partial approach (2-step) was similar to CCR; their CCR approach was more aggressive than the one we propose to use, excavating “hard” dentine. Therefore, more evidence is needed about the performance of a minimally invasive option of SCR in the NHS and about whether dentists will adopt it. There is one ongoing trial in France [20] looking at this research question in a secondary care setting. Personal communication with the trial team confirmed they had experienced a merger (contamination) of the two technologies (i.e. the two techniques undertaken by an individual dentist tended to become more similar dependent upon their initial skills and preferences). The trial has had more than 30% loss to follow-up. The authors believe that is due to the secondary care setting where patients are usually transient and short term. Our research robustly monitors and minimises the risk of the technologies merging, and most patient participants are routine attenders at their dental practice.

Therefore, this research is important to establish whether SCR will sustain tooth vitality and reduce the need for complex, costly treatment including root canal treatment, crowns, extractions, bridgework or implants [21]. In addition to potential cost savings, this reduced treatment need would be expected to improve quality of life and reduce anxiety and stress.

The risk to participants is low as both treatments are utilised in NHS practice albeit that SCR is relatively under-employed. For SCR, which is a minimally invasive treatment, the perceived risk is the residual caries alone may lead to further deterioration of the tooth. The risks from CCR are already managed within existing dental practice so the trial does not impose any new risks. Risk in both arms will be monitored as part of the trial as the primary and some secondary outcomes directly measure the impact of each treatment.

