### Outcomes from data linkage with routine administrative NHS health records

Dataset: Management Information and Dental Accounting System (MIDAS) [27] collated information on all child and adult primary care dental practice appointments and treatments in Scotland (including Childsmile practice prevention items)**.**

Trial participant data will be linked to individual health records from MIDAS database, tooth-specific data on specific treatments (restorations, root canal therapy, and extractions).

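### Extraction counts as a primary event only when the treating dentist attributes it to loss of vitality; other extractions are censored, no clinical outcome covers any-cause loss of the trial tooth, and the routine records described for validation give no reason

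*Protocol article*

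**What the plan says.** Under Clinical outcomes, the event time is the "time from randomisation to root canal treatment or extraction due to loss of vitality, the primary time point of interest is three years". The next sentence adds a further condition for vitality, "the absence of clinical signs and symptoms of pulp death including evidence from radiographs". I read the restriction by cause as attaching to extraction. If it was meant to cover root canal treatment too, the wording should say so.

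Under Missing data, "Participants with no event will be censored at their last visit with sustained tooth vitality". No separate rule is given for a tooth extracted for a reason other than loss of vitality. The analysis section plans a Cox model and a graph of the estimated survivor function.

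The section on day-to-day management gives the practice dentists responsibility for all clinical outcome assessment. Under Clinical outcomes, only the reading of radiographs is described as blinded.

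On routine data, the linkage section describes "tooth-specific data on specific treatments (restorations, root canal therapy, and extractions" and mentions no reason for treatment. The Missing data section plans a validation of the primary CRF outcome against tooth-level routine data, and adds: "Routinely collected data will be considered to supplement missing outcome data if deemed appropriate". The sample size section cites Scottish teeth of which "6.6% had received further endodontic treatment or were extracted at 3 years follow-up", again without cause.

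**The concern.** Dentists cannot be masked to the amount of caries they remove. With about 65 practices and up to 75 clinicians, the dentist who later extracts the tooth will often be the one who treated it. When a tooth is lost, that dentist's view of the cause decides whether it is a failure or a censored success. If attribution leans one way by arm, the primary hazard ratio moves with it, and no listed analysis would show this.

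The Background gives fewer extractions as one purpose of selective removal, without restricting them by cause, and says of that approach that "the perceived risk is the residual caries alone may lead to further deterioration of the tooth". A reader will want to know whether more trial teeth were kept. Clinical secondary outcomes cover pulp exposure, caries progression and restoration failure with re-restoration, but not any-cause tooth loss.

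The validation has a related problem. If routine records show an extraction and the CRF records it as unrelated to vitality, the two sources disagree under the primary definition although both are correct. Agreement would look worse than the data deserve, and that result bears on whether routine data are used further.

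**Working it through.** **1. How a lost trial tooth is classified under the article's wording**

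| What happens to the tooth | Primary analysis | Routine record as described |
|---|---|---|
| Root canal treatment | Event | Root canal therapy |
| Extraction attributed to loss of vitality | Event | Extraction |
| Extraction for another reason, signs of pulp death recorded | Not vital under the second sentence of the definition | Extraction |
| Extraction for another reason, no such signs | Censored at last vital visit | Extraction |

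The second and fourth rows differ in the primary analysis only through the recorded reason and signs. In the routine record they are identical.

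**2. The routine figure behind the control rate**

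6.6% × 3 = 19.8%, which matches the assumed 20% failure under complete removal. The 6.6% includes extraction with no cause stated, whereas the endpoint restricts extraction by cause. The factor of three is an openly stated judgement about lesion depth.

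**3. Size, by assumption only**

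Inputs from the article: vitality failure at three years of 17% (complete removal) and 8% (selective removal), from the 83% and 92% in the sample size section. Under exponential survival the vitality hazard ratio is ln(0.92)/ln(0.83) = 0.447. The article prints 0.42; that difference is a separate matter.

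Assumed, because the article gives nothing: other-cause extraction q, independent of vitality failure. Any-cause survival = (1 − vitality failure) × (1 − q); hazard ratio = ln(S selective)/ln(S complete).

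Complete removal, q = 2%: 0.83 × 0.98 = 0.813, failure 18.7%.

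| q, selective removal | Any-cause failure, selective | Difference (points) | Any-cause HR |
|---|---|---|---|
| 1% | 8.9% | 9.7 | 0.45 |
| 2% | 9.8% | 8.8 | 0.50 |
| 4% | 11.7% | 7.0 | 0.60 |
| 6% | 13.5% | 5.1 | 0.70 |

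The vitality hazard ratio stays at 0.447 in every row.

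**4. The survivor curve**

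With constant hazards, the cumulative incidence of vitality failure is [ln(1 − vitality failure)/ln(S any-cause)] × (1 − S any-cause).

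- Complete removal, q = 2%: (0.1863/0.2065) × 18.66% = 16.8%, against 17.0% from a curve that censors other-cause extractions.
- Selective removal, q = 6%: (0.0834/0.1453) × 13.52% = 7.8%, against 8.0%.

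The censoring curve overstates the risk of vitality failure by about 0.2 points at these rates. The direction is certain. The amount is small while other-cause extraction is uncommon.

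**The case against.** The case for leaving the plan alone has real force, and much of it stands.

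- **The endpoint is a proper choice.** The trial asks about vitality, and 99% of surveyed practitioners thought the primary outcome important. An extraction unrelated to the pulp is not loss of vitality. This stands, and the point does not ask for a different primary endpoint.
- **A reader might infer that the Cox result is biased because other-cause extractions are censored.** It is not, on that ground alone. Censoring a competing event is a standard way to estimate a cause-specific hazard ratio. The caution applies to the survivor curve.
- **A reader might infer that the endpoint conceals the very risk named for selective removal.** The Background speaks of deterioration from residual caries. It does not name restoration breakdown or extraction of a vital tooth, and it says that removing less tissue lowers fracture risk. Teeth with signs of pulp death fail anyway. Caries progression and restoration failure are time-to-event secondary outcomes, and tooth loss is an example state in the economic model. Structural failure would be partly visible.
- **Excess extraction under selective removal is unsupported.** The nearest cited figure, for the related outcome of restoration failure, is OR 0.97 [0.64–1.46]. The 4% and 6% rows are illustrations, not expectations.
- **Supplementation is conditional,** and its detail is left to a data linkage analysis plan. A reader might infer that supplemented participants will fail on any extraction. The article does not say so.
- **The Discussion describes blinded outcome evaluation.** The only blinding it specifies elsewhere for outcomes is of radiographs. The cause of an extraction is recorded by the dentist.

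What remains is the dependence on unblinded attribution, the lack of an any-cause clinical outcome, and a validation between unlike definitions. These follow from what the article itself fixes, so they are not merely detail left to an unseen analysis plan.

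**Conclusion.** The point holds as a limited one. The vitality endpoint can stay, and its hazard ratio is interpretable as cause-specific. But the result depends on cause attribution by an unmasked dentist, the planned survivor graph would overstate vitality-failure risk if other-cause extractions are censored, and the validation would compare a cause-restricted CRF event with records described without reasons.

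The routine 6.6% is only loose confirmation of the control rate. A reader might infer that 80% is therefore wrong and that power falls. The article does not support that: "The control rate of 80% is based upon the existing evidence base, clinical experience and confirmed by Scottish tooth-level routine data". It also cites a published vitality rate of about 80% at three years. Cutting the 6.6% while holding the factor of three fixed would change one part of a combined judgement and prove nothing about the whole.

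The size of any effect is unknown. The range of 0.45 to 0.70 for the any-cause hazard ratio rests on assumed extraction rates, on independence, and on the planned 17% and 8%. That the routine figures cover all causes is inferred from the absence of any stated cause.

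**What to change.** 1. Keep sustained tooth vitality as the primary endpoint.
2. Pre-specify a supportive time-to-event analysis, by arm, of any root canal treatment or any extraction of the trial tooth, whatever the reason. For extractions, this removes the dependence on attributed cause.
3. In the vitality analysis, treat extraction for another reason as a competing event dated at the extraction, not censored at the last vital visit. Show cumulative incidence by arm in place of, or beside, the survivor curve. The cause-specific Cox model can remain.
4. Run the CRF-versus-routine validation on the any-cause definition, so that both sources count the same thing.
5. If routine data supplement the primary endpoint, limit this to root canal treatment and to extractions whose reason can be established. Root canal records remain usable.

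No new data are needed, because the CRF already records the reason for and detail of treatment to the trial tooth. The cost is analysis-plan wording, one extra analysis, and a second event definition to report.
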